## Abstract

**Background:**

The level of physical activity undertaken by stroke survivors living in the community is generally low. The main objectives of the *IMPACT* trial are to determine, in individuals undergoing rehabilitation after stroke, if 8 weeks of high-intensity treadmill training embedded in self-management education (i) results in more physical activity than usual physiotherapy gait training and (ii) is more effective at increasing walking ability, cardiorespiratory fitness, self-efficacy, perception of physical activity, participation, and health-related quality of life as well as decreasing cardiovascular risk, and depression, at 8 and 26 weeks.

**Methods:**

A prospective, two-arm, parallel-group, randomised trial with concealed allocation, blinded measurement and intention-to-treat analysis, will be conducted. 128 stroke survivors undergoing rehabilitation who are able to walk independently will be recruited and randomly allocated to either the experimental or control group, who will both undergo gait training for 30 min, three times a week for 8 weeks under the supervision of a physiotherapist. Outcomes will be measured at baseline (Week 0), on completion of the intervention (Week 8) and beyond the intervention (Week 26). This study has obtained ethical approval from the relevant Human Research Ethics Committees.

**Discussion:**

Improving stroke survivors’ walking ability and cardiorespiratory fitness is likely to increase their levels of physical activity. Furthermore, if education in self-management results in sustained high levels of physical activity, this should result in improved participation and quality of life.

**Trial registration:**

This trial was registered with the Australian New Zealand Clinical Trials Registry (ACTRN12613000744752) on 4th July, 2013.

## Background

Stroke survivors have three times the risk of further cardiovascular events than the general population [1, 2]. There is strong evidence that physical activity has a protective effect against stroke [3, 4], it can reduce cardiovascular risk factors in people with stroke [5] and not undertaking enough physical activity increases the risk of recurrent stroke [6, 7]. The level of physical activity undertaken by stroke survivors living in the community is generally low [8, 9]; less than half that of age-matched adults [10, 11]. However, increasing the level of physical activity after stroke is challenging, perhaps because multiple factors contribute. For example, lack of physical activity is correlated with poor cardiorespiratory fitness [12], reduced walking ability [13] and low self-efficacy [14].

High-intensity treadmill training, i.e., training to a target heart rate around 40–60% of heart rate reserve, has been shown to increase cardiorespiratory fitness in people with chronic stroke [15, 16]. However, this type of training is not usually started during inpatient rehabilitation. In a pilot study, we have shown that high-intensity treadmill training during inpatient rehabilitation is feasible, is not detrimental to the walking pattern and may result in an improvement in walking ability [17]. However, we have not shown that it increases cardiorespiratory fitness.

Furthermore, one of the main findings of studies investigating interventions to improve cardiorespiratory fitness after stroke, is that the benefit is only partially maintained beyond the period of intervention [15]. It is therefore important to support stroke survivors to exercise independently in the long term [18]. A self-management approach to rehabilitation has been recommended as a strategy to optimise outcomes for stroke survivors after discharge from hospital [19]. Interventions that are grounded in health behaviour theory, and which target psychological constructs with evidence based intervention activities, are more successful than those which are neither theory- nor evidence-based [20]. The Health Action Process Approach (HAPA) has been found to be useful, particularly in the rehabilitation setting, for predicting and explaining changes in health behavior [20]. It consists of two phases – a motivational phase and a volitional phase. In the motivational phase, the perception that a person is at risk, their positive outcome expectancies for completing a certain behaviour, and their perceived self-efficacy for performing a certain action interact to drive the formation of a behaviour intention [20]. In the volitional phase, self-regulatory skills and strategies (action planning, coping planning, recovery self-efficacy and social support) are employed to translate intentions into action [20]. Intervention behaviour change techniques can be tailored to participants dependent on their phase. The validity of the HAPA has been tested in the intervention context with people in the rehabilitation setting, including individuals with stroke [21, 22] and could be useful to address the behavior change issue of modifying physical activity after stroke. To augment this approach, goal setting theory can be employed to target goal difficulty and specificity [23].

It appears that a comprehensive, patient-centered, goal-oriented approach to lifestyle modification is required early in rehabilitation that addresses both the ability for stroke survivors to be active, and the motivation to do so. Maintaining high levels of physical activity via improved walking ability and ongoing cardiorespiratory fitness should also confer a range of benefits, such as an improvement in self-efficacy, participation, and health-related quality of life and a decrease in cardiovascular risk [24], and depression. If a sufficient training level can be reached, there is likely to be an impact on lipid profile: high sensitivity C- reactive protein (HSCRP), total cholesterol (TC), triglycerides (TRG) high density and lipoprotein cholesterol (HDL-C) and low density lipoprotein cholesterol (LDL-C). The link between modification of the lipid profile and inflammatory biomarkers to carotid intima–media thickness and subsequent cerebro and cardiovascular events has been convincingly demonstrated [25]. Additionally, there is strong evidence that moderate intensity exercise can improve lipid profiles and inflammatory markers, including highly sensitive C-reactive protein (HSCRP), an independent predictor of cardiovascular events in both primary and secondary prevention [26–29]. However, until recently it has been difficult to exercise stroke patients (who due to their pathophysiology are already at risk of future cardiovascular events), at a sufficient level to achieve these benefits. A recent study [30] has provided the first evidence that high-intensity treadmill training in chronic stroke survivors reduces cardiovascular risk markers (cerebral vasomotor reactivity), implying that this form of exercise intervention may confer a neuroprotective effect. High-intensity treadmill training may lower cardiovascular disease risk factors for stroke survivors which in turn should result in secondary prevention of future cardiovascular and cerebrovascular events.

We are therefore conducting a randomized trial investigating the effect of high-intensity treadmill training during inpatient rehabilitation embedded in self-management. This will be compared with usual physiotherapy gait training to ensure a similar volume of training. The main objectives of the *IMPACT* trial are to determine, in individuals undergoing rehabilitation after stroke, if 8 weeks of high-intensity treadmill training embedded in self-management:(i)results in more physical activity than usual gait training; and(ii)is more effective at increasing walking ability, cardiorespiratory fitness, self-efficacy, perception of physical activity, participation, and quality of life as well as decreasing cardiovascular risk, and depression; immediately after the intervention at 8 weeks and beyond the intervention at 6 months.

## Methods

A prospective, two-arm, parallel-group, randomised trial with concealed allocation, blinded measurement and intention-to-treat analysis will be undertaken with stroke survivors undergoing rehabilitation (Fig. 1). Participants will be recruited from rehabilitation units in two states (Queensland and NSW) in Australia. A list of centres is available on the trial registry. Participants will be randomly allocated to two groups. Gait training for the experimental group will be high-intensity treadmill training plus self management and for the control group will be usual gait training. Both groups will have the same amount of time spent on gait training. To minimise the risk of contamination, the experimental group will receive their intervention from a different therapist in a different location from the control group. The rest of the multi-disciplinary rehabilitation program will be unchanged. The end point of the intervention phase of the study will be 8 weeks and the end point of the follow-up phase will be 26 weeks. Outcomes will be measured at baseline (Week 0), on completion of the intervention (Week 8) and beyond the intervention (Week 26). Both data collection and data analysis will be completed by researchers who are blind to group allocation. Participants will be asked not to reveal the nature of their intervention to measurers. It is not possible to blind participants or therapists to group allocation. The study protocol has been approved by the appropriate Human Research Ethics Committees and has been registered on the Australian New Zealand Clinical Trials Registry.

**Fig. 1 Fig1:**
[figure not shown]
Design of the study

### Participants, therapists, centres

Individuals with stroke will be screened and invited to participate if they are: within two months of a stroke (confirmed by CT scan or clinical diagnosis); aged 18 years or older; able to walk 10 m independently (without physical assistance but with or without an aid); and able to follow three-stage commands. They will be excluded if they: were unable to walk independently prior to current stroke; have co-morbidities relating to the lower limbs that might limit their walking (such as arthritis); have unstable cardiac status (which would preclude them from participating in intensive training); unable to return for assessment or training; or are unable to provide informed consent. Information that will be collected to describe the sample will include: age, sex, description of the stroke (time, side affected, type, location, severity), aphasia, recombinant tissue plasminogen activator (rt-PA), medications, co-morbidities, and previous living arrangements.

Therapists delivering the intervention will be included if they are physiotherapists with more than 5 years clinical experience, or experience in treadmill training or self-management.

Centres will be included if they contain a rehabilitation unit that has a throughput of stroke of more than 50 per year.

### Randomisation

Randomisation will be computer-generated, independent and concealed. The allocation sequence has been computer-generated by an independent researcher not involved in this study. For each centre, allocation to the experimental or control group will occur in random permuted blocks, so that after every block (of 4–6 participants), the experimental and control group will contain equal numbers [31]. Group allocation is stored in numbered, opaque envelopes in order to provide secure randomisation. After baseline measures have been collected, the therapist providing the intervention opens the envelope and reveals the group allocation. In this way, the allocation sequence is concealed from on-site recruiters.

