### Sample size

One hundred twenty eight participants will be recruited. The sample size has been calculated to be able to detect an effect size of 1200 steps/day with 80% power at a two-tailed significance level of 0.05. This between-group difference was based on an estimate that participants would take 4000 (SD 2000) steps/day at baseline and that the control intervention would increase this to 5200 step/day and the experimental intervention would increase this to 6400 steps/day, putting them above a sedentary level for older adults [54]. The smallest number of participants to detect a difference in physical activity of 1200 steps/day between two groups estimated from independent samples is 55 participants per group. On the assumption from previous trials with this population that approximately 15% of the participants may be lost to follow up during the course of the study, we have set a target of 128 participants in total. In order to reach the target sample size, the trial will be carried out across multiple centres, and a researcher will be employed to screen all stroke survivors at each centre.

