### Statistical analysis

Primary and secondary outcomes including physical activity, walking ability, cardiorespiratory fitness, cardiovascular risk, self-efficacy, perception of physical activity, participation, and quality of life will be reported as point estimates and measures of variability. An intention-to-treat between-group analysis will be performed on all outcome measures. Between-group differences will be analysed using generalized mixed effects models for continuous data, since this analysis does not require casewise deletion due to missing data. Data will be presented as mean difference (95% CI). Baseline characteristics judged to be clinically different between groups may be included as covariates.

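### Allocation is blocked within centre, but the analysis section names no centre term, and its only stated adjustment rule would not normally bring centre in

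*Protocol article*

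**What the plan says.** Under Randomisation, the protocol article states: "For each centre, allocation to the experimental or control group will occur in random permuted blocks". Each block has 4 to 6 members, and the two arms are the same size whenever a block is complete. The Sample size section adds that "the trial will be carried out across multiple centres". The Methods section places these centres in two Australian states. The number of centres is not given in the text.

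Under Statistical analysis, it states: "Between-group differences will be analysed using generalized mixed effects models for continuous data". The reason given for this choice is that such a model keeps participants with missing data; stratification and clustering are not mentioned. The only sentence on adjustment is: "Baseline characteristics judged to be clinically different between groups may be included as covariates". No fixed or random terms are listed, so centre is neither included nor excluded.

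**The concern.** Blocking within centre removes differences between centres from the treatment comparison, so the treatment estimate varies less than it would under simple randomisation. An analysis obtains that benefit only if it also takes between-centre variance out of its error term. Otherwise the model's standard error describes a noisier trial than the one that was run: confidence intervals are too wide, the test rejects less often than its nominal level under the null, and some power is lost.

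The stated covariate rule works against the design here. It looks for observed differences between groups, whereas the reason to adjust for a stratum is that the design has balanced it. With blocks of 4 to 6, the arms at any centre can differ at randomisation by at most half a block, that is by 2 or 3 participants. Centre would therefore rarely be judged different between groups.

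Centre could well matter for steps/day. Control gait training is quantified but not prescribed, and the rest of the rehabilitation programme is not controlled, so local practice can differ.

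**Working it through.** **Inputs from the Sample size section.** The design is "able to detect an effect size of 1200 steps/day with 80% power at a two-tailed significance level of 0.05". The SD comes from the estimate that "participants would take 4000 (SD 2000) steps/day at baseline". The stated number needed "is 55 participants per group", raised to 128 in total for about 15% loss.

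**The plan's own figure.** n per group = 2 × (1.960 + 0.842)² × (2000/1200)² = 43.6, so 44 (45 with the exact noncentral t). The stated 55 is not reproduced. It would need an SD of about 2246, and the stated 2000 is a baseline SD, so another SD may have been used. This does not bear on the present point. It does mean that, on the stated inputs, 55 per group has about 88% power. After 15% loss, 128 × 0.85 = 108.8, or 54.4 per arm, which is close to 55.

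**Assumed input.** The centre ICC, the share of outcome variance lying between centres, is not in the document. Values from 0 to 0.20 are assumed.

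**Analytic check for a single-time-point comparison with centre omitted.** After blocking, the true variance of the treatment estimate carries only the within-centre share, 1 − ICC, while the unadjusted model uses the whole variance. Hence:

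- SE overstatement = 1/√(1 − ICC)
- actual type I error at nominal 0.05 = 2 × [1 − Φ(1.96/√(1 − ICC))]
- power without centre = Φ[(0.6 × √(54.4/2) − 1.96)/√(1 − ICC)]
- power with centre = Φ[0.6 × √(54.4/2)/√(1 − ICC) − 1.96]

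Here 0.6 = 1200/2000, and 0.6 × √27.2 = 3.129.

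| Assumed ICC | SE overstated by | Actual type I error | Power without centre | Power with centre |
|---|---|---|---|---|
| 0 | 0% | 0.050 | 0.879 | 0.879 |
| 0.05 | 2.6% | 0.044 | 0.885 | 0.894 |
| 0.10 | 5.4% | 0.039 | 0.891 | 0.910 |
| 0.20 | 11.8% | 0.028 | 0.904 | 0.938 |

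At an ICC of 0.01 the overstatement is 0.5% and the actual error 0.049.

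**Simulation check.** 4000 trials per setting, 110 participants, blocks of 4 or 6 within equal-sized centres, total SD 2000, and a linear model at one time point with and without centre. The numbers of centres (4 and 8) are assumed.

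| Centres | ICC | Mean model SE without / with centre | Type I error without / with | Power without / with |
|---|---|---|---|---|
| 4 | 0.05 | 378 / 371 | 0.045 / 0.048 | 0.885 / 0.892 |
| 4 | 0.10 | 376 / 362 | 0.045 / 0.050 | 0.893 / 0.906 |
| 4 | 0.20 | 370 / 340 | 0.034 / 0.048 | 0.903 / 0.935 |
| 8 | 0.20 | 376 / 341 | 0.028 / 0.047 | 0.899 / 0.932 |

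In the last row the empirical SE of the unadjusted estimate was 340, against a model SE of 376. The simulated SE overstatement at an ICC of 0.20 is 370/340 = 1.09 with 4 centres and 376/341 = 1.10 with 8. Both are below the analytic 1.118, so the analytic figures are best read as upper limits.

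**Where the direction reverses.** If the treatment effect itself varies between centres (assumed between-centre SD of 600 steps/day, ICC 0.05, mean effect zero), the model without centre rejected in 12% of trials with 4 centres and 7.5% with 8. Adding a centre intercept did not cure this: the rates were 12.9% and 8.7%.

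**The case against.** The strongest reply is that the article is silent on model terms altogether. It lists no time, group-by-time, baseline, participant or centre effect. A mixed model can easily carry a centre effect, and a journal article commonly leaves such lists to the full protocol or analysis plan, which are not shown. The covariate sentence is permissive, contains no word limiting adjustment to that route, and is about participants' baseline characteristics rather than design factors. This stands as a limit. A reader might infer that the model excludes centre, or that centre could never enter it; the document supports neither. What remains is that the article does fix one adjustment rule, and that rule runs contrary to how a blocking factor should be handled.

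A second reply is that the arithmetic fits a comparison at one time point without baseline. Steps/day is measured at Weeks 0, 8 and 26. With a participant random intercept and a group-by-time contrast, a centre effect that is constant over time cancels from within-person change, and baseline adjustment would absorb part of it. This also stands: for the primary outcome the figures are closer to a ceiling. The relief is less available for self-efficacy, depression, perceived activity, participation and quality of life, which the Measurement section lists at Weeks 8 and 26 only.

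A third reply is that the harm is small and, under a common treatment effect, on the safe side. That is correct.

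**Conclusion.** The point holds in conditional form. Randomisation is stratified by centre, and the analysis as described does not commit to reflecting that. If centre is omitted, is prognostic, and the treatment effect is broadly common across centres, inference is mildly conservative. At an assumed ICC of 0.05 to 0.20, the overstatement of the standard error is at most about 3% to 12% and the loss of power about 1 to 3 percentage points for a single-time-point comparison. It is less where baseline or within-person change is modelled, and nil at an ICC of 0.

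A reader might go further and infer that the trial's standard errors are too large as a matter of fact, or that the trial is underpowered. The document does not support either reading. It gives no ICC, and power without centre stays at about 88% to 90% on the stated inputs, above the planned 80%. Nor does omitting centre raise the false-positive risk under a common effect. Effects that differ between centres could raise it, but that is a separate matter which a centre intercept does not solve. This is a free improvement to the plan; it does not call the trial's validity into question.

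**What to change.** State in the analysis section that centre, as the randomisation stratum, enters the primary and all secondary models as a fixed or random effect regardless of observed balance, and that the imbalance-driven covariate rule does not govern it. Set a rule for pooling very small centres before unblinding. If the full plan already contains such a term, a sentence saying so is enough. The cost is one model term and a few lines of text; no new data and no change to the sample size are needed.

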### Intervention

Both the experimental and the control group will undergo gait training during rehabilitation as part of this trial for 30 min, three times a week for 8 weeks under the supervision of a therapist. Gait training for the other part of the week will be as usual. The gait training may be carried out across inpatient and outpatient departments – since some participants may be discharged home before the end of the 8-week training. No other part of the multidisciplinary rehabilitation program will be controlled. Randomisation should ensure that any effect of other interventions will be the same for both groups, therefore, other rehabilitation will not be withheld. Typically for stroke patients, rehabilitation broadly consists of as much physical practice as possible including early mobilisation and upper limb training as specified by the *Clinical Guidelines for Stroke Management 2010* [32].

#### Experimental group

The experimental group will receive high-intensity treadmill training and self-management education. The high-intensity treadmill training will be based on our pilot program [17] of up to 30 min walking on a treadmill at an intensity of 40–60% heart rate reserve or a Borg Rating of Perceived Exertion [33] of 11–14; the minimum required for training cardiorespiratory fitness [34]. Target heart rates will be calculated according to Karvonen method [34] adjusting for beta-blockers for those taking heart rate lowering medication. Participants will start at an intensity of 40% heart rate reserve, progressing each week by a 5–10% increase until 60% heart rate reserve is reached. Heart rate will be recorded via a portable heart rate monitor. While on the treadmill, participants will be encouraged to hold the handrail and a physiotherapist will provide assistance as required to ensure foot clearance during swing phase. In addition, an assistant will be available to operate the controls and the safety stop cord will be attached to participants at all times.

The self-management education in this intervention is underpinned by two theoretical models: the Health Action Process Approach (HAPA) [35] and Goal Setting Theory [36]. At the beginning of the study, participants in the treadmill training group will receive a detailed workbook to complement the treadmill training component of the intervention. The workbook will serve a dual purpose of encouraging self-monitoring of physical activity and guiding participants through the process of setting short- and long-term goals as well as formulating action plans and coping strategies. The therapist delivering the intervention will allocate a proportion of each treadmill session to addressing the self-management-related tasks outlined in the workbook. The multi-modal behaviour change techniques to be employed have been selected to align with the theoretical basis of the intervention and progress over time. These include: education, behavioural instruction, self-monitoring, goal setting and goal review, feedback, problem solving, action planning and coping planning. The way in which these behaviour changes strategies are operationalized is described below. In order to address risk perception and outcome expectancies, participants will be informed about the consequences of their action (inaction) and asked to consider the costs and benefits of their behaviour. Task self-efficacy (for treadmill walking and physical activity generally) will be enhanced by providing instruction on how to perform the behaviour, prompting of self-monitoring (using the workbook), and the provision of feedback on performance. Participants will be asked to set specific, relevant and patient-centred short- medium- and long-term goals as a way of fostering intention formation. Action planning and coping planning (i.e., problem solving and identifying strategies to overcoming potential barriers to achieving behaviour change goals) will be used to build self-efficacy for behaviour maintenance. As participants reach the end of the treadmill intervention, and transition to independent physical activity practice, further strategies to encourage maintenance self-efficacy will be employed. These will include discussions to prompt participants to review their behavioural goals and gather information on alternative options to incorporate sufficient physical activity program in their life.

Physiotherapists delivering the experimental intervention will be trained in high-intensity treadmill training and self-management education and provided with guidelines, training manuals and support. Information describing the high-intensity treadmill training (e.g., duration, distance walked, observed heart rate, perceived exertion, adverse events) and self-management education (e.g. frequency of participant-initiated conversations on coping planning) will be recorded to be able to describe the intervention accurately. Adherence to the experimental intervention will be monitored by reviewing the recording sheets and by auditing 1–2 sessions per therapist.

